### Power/effect size analysis

With the pre-specified sample size of 250 sites and design (wedge design with four strata/waves starting 3 months apart), we investigated the intervention effects under each of the primary hypotheses in Aim 1, that are detectable with at least 80 % power of a two-sided significance test with *α* = 0.05 (Appendix). Conversely, we assessed the power to detect effects that are clinically meaningful and realistic. For each of the four outcomes, we are interested in the proportion of eligible patients in a site who meet guideline recommendations for ABCS clinical care in the fourth quarter of the PF intervention (i.e., month 12 of the intervention) relative to compliance proportions at baseline.

Using conservative (i.e., low) eligibility levels of an average of 50 patients per physician per quarter, we will have over 80 % power to detect a 2.0 % change, assuming a starting compliance rate of 20 % (increasing from 20.0 to 22.0 %). Finally, we have little information to estimate the current levels of variation between sites (*σ*
_*b*_^2^). However, the simulations suggest that power does not decrease when the assumed variance is increased from 0.10 to 0.25 on the log scale. If in fact the variance is lower, closer to 0.01 or 0.05, power is increased substantially to over 95 %.

#### Aim 2

We will identify baseline organizational characteristics (e.g., site level adaptive reserve, organizational change capacity) that are associated with primary outcomes. This will be accomplished by including separately each organizational characteristic in the main models used under Aim 1 as a main effect and in interactions with the PF indicator. We will conduct a further analysis to explore the possibility that changes in organizational level factors mediate the effect of the intervention on the primary compliance outcomes. Mediation analysis methods in the context of a stepped-wedge design have not been well developed. We will conduct a preliminary analysis to assess if the intervention is associated with changes in site level adaptive reserve, organizational change capacity, and practice changes (assessed with the practice change survey). If there is a detectable effect of the intervention on the organizational level factors, we will assess whether the changes in these organizational level factors are associated with changes in the primary compliance outcomes using the Baron and Kenny “product method” as a starting point of the analysis [38]. If necessary, we will explore more complex structural equation models (SEM) adapted for Poisson outcomes as well as more recently developed causal inference mediation methods to evaluate the mediation.

#### Aim 3

We will use qualitative methods to conduct a more in-depth assessment of internal and external context including barriers and facilitators (among high and low performers) to implementing practice change and achieving ABCS outcomes. The transcriptions of the interviews and focus groups will be coded using Atlas.ti. The coding scheme will be developed by the evaluation team to focus on key dimensions identified both a priori (i.e., from the interview and focus group protocols) and those that emerge during site visits, interviews, and focus groups. Two coders will independently code at least 10 interviews and all focus groups. Double coding will continue until adequate inter-rater reliability is achieved.

Most of the quantitative data will be analyzed descriptively to provide documentation and description of the practices, the implementation components, fidelity, and context. Using the score calculated from the practice change survey, we will evaluate changes over time in implementation of the practice change components (i.e., one component of implementation fidelity) with repeated measures ANOVA. We will also explore the association between implementation fidelity and primary outcomes (Aim 1 and 2 analyses).

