### Analysis plan

#### Aim 1

The primary outcomes are the proportion of patients who reach clinical goals based on national guidelines for (a) aspirin use, (b) HTN control, (c) blood cholesterol management, and (d) smoking cessation assistance at the end of the intervention (12 months) period and 6 months post-intervention. Each of the four hypotheses referring to the four primary outcomes will be tested separately with a two-sided test with *α* = 0.05, i.e., no adjustment for multiple testing will be applied. The analysis of effect of PF on the ABCS outcome measures in the context of a stepped-wedge design will be based on a generalized linear mixed model (GLMM). In particular, to assess the intervention effect, we will use a Poisson model with random site and provider within site effects. Each model will be as follows:1$$ \log \left({C}_{it}\right)=\mu +{\beta}_1t+{\beta}_2{I}_{it}^{PF}+{\beta}_3{I}_{it}^{PF}\left(t-{s}_i\right)+\gamma {Z}_i+{b}_i+ \log \left({E}_{it}\right), $$

where *C*
_*it*_ is the number of patients in site *i* who (a) had received aspirin, (b) had controlled blood pressure, (c) had controlled cholesterol, or (d) received smoking cessation counseling during period *t*, for *t* ∈ (0, 1, …, 11). Each period is 3 months, and *t* = 0 is the baseline quarter. *I*
_*it*_^PF^ is an indicator variable, and *I*
_*it*_^PF^ = 1 if site *i* has been assigned to the PF intervention at period *t*, *I*
_*it*_^PF^ = 0 otherwise. *s* is the time period when the PF intervention begins for site *i. Z* is a site-level indicator variable, *Z* = 1 if site *i* has three or more providers, *Z* = 0 otherwise. *E*
_*it*_ is the number of patients at site *i* who were eligible to be counted during period *t*. The eligible pool of patients *E*
_*it*_ will be different for each outcome and has been described in detail in Table 1. Log(*E*
_*it*_), considered the “offset” in the Poisson regression model, is a random effect for site *i* with mean 0 and variance *σ*
_*b*_^2^. The estimation via model (1) takes into account a general time trend and allows for the intervention effects to grow over time following implementation of the intervention.

Our primary outcome of interest for each of the four models is proportion of patients who meet clinical goals (described above) at 12 months. In each model, this effect (after taking into account general time trends) would be captured by *β*
_2_ + 3*β*

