## Appendix

### Power/effect size analysis

With the pre-specified number of sites (250) and design (wedge design with four strata starting 3 months apart, we investigate the intervention effects under each of the primary hypotheses in Aim 1, that are detectable with at least 80 % power of a two-sided significance test with *α* = 0.05. Conversely, we assess the power to detect effects that are clinically meaningful and realistic.

For each of the four outcomes, we are interested in comparing the proportion of eligible patients in a physician’s panel who meet compliance (i.e., appropriate blood pressure level, appropriate cholesterol level, indication that aspirin was recommended, and indication of referral for smoking cessation) in the third quarter after PF intervention with the compliance proportion at baseline. In particular, we are interested in the difference *d*
_*π*_ = *π*
_3_ − *π*
_0_, where *π*
_0_ is the baseline compliance rate, and *π*
_3_ is the third period compliance rate. The proportions *π*
_0_ and *π*
_3_ will be estimated by *C*
_0_/*E*
_0_ and *C*
_3_/*E*
_3_, respectively, where *C* is the number of patients in compliance and *E* is the number of eligible patients. We will use the model to estimate the difference *d*
_*π*_. However, because of the specific Poisson distributions of the data and the model that we will be using, the treatment effect is more naturally expressed as a ratio rather than a difference: *r*
_*π*_ = *π*
_3_/*π*
_0_.

We conducted the simulations varying the ratio *r*
_*π*_, but for the clarity of interpretation, we also present the effect as a difference *d*
_*π*_. Our goal is to find the *r*
_*π*_ ’ s (and *d*
_*π*_ ’ s) that would allow 80 % power of a two-sided test for significance with *α* = 0.05. We simulate the outcomes based on different assumptions about baseline compliance rates, random effects (which are at the scale of log(*C*)), and patient eligibility numbers. For each set of assumptions, 2000 data sets were generated using the GLMM model given in Eq. (2).

2 $$ \log \left({C}_{jt}\Big|{d}_j\right)=\mu +{\beta}_1t+{\beta}_2{I}_{jt}^{\mathrm{PF}}+{\beta}_3{I}_{jt}^{\mathrm{PF}}\left(t-{s}_j\right)+\gamma {Z}_j+{d}_j+ \log \left({E}_{ijt}\right), $$

The rate ratio *r*
_*π*_ is a function of baseline treatment effect (*β*
_2_) and time-related treatment effect (*β*
_3_) : *r*
_*π*_ = exp(*β*
_2_ + 2*β*

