_3_). For each of the 1000 data sets, we estimated the same model and tested the hypothesis that *β*
_2_ + 2*β*
_3_ (the effect size in the third quarter) was significantly different from 0. The proportion of significant results represented the power of the study under the specific set of assumptions.

For the purposes of simulation, we assumed 63 sites in each stratum, for a total of 252 sites. Preliminary simulations indicated that larger general time trends (*β*
_1_) and larger number of patients in a physician panel both increased power. Based on this, our final simulations included very conservative assumptions of zero growth trend (*β*
_1_ = 0) and average eligibility size (*E*
_*jt*_) of 50 patients per physician at the practice. In the simulation, a general level of *E*
_*j*_ for site *j* was generated from a Poisson distribution of mean 50 × the number of physicians at the site. The value of *E*
_*jt*_ for a particular time period was calculated (and rounded to the nearest integer) as *E*
_*ij*_ + *e*
_*ijt*_, where *e*
_*ijt*_ ~ *N*(mean = 0, sd = 2). For each site *j* during period *t*, log(*C*
_*jt*_) was generated using equation (2). A value *C*
_*jt*_, the number of patients in compliance for site *j* during period *t* was generated from a Poisson distribution with mean *C*
_*jt*_.

Table 4 shows results after varying effect size parameters (*β*
_2_ & *β*
_3_), baseline compliance rate (*π*
_0_), site-level random effect variance (*σ*
_*d*_^2^), and patient eligibility levels (*E*). The current baseline compliance rates for the four measures are 49 % (blood pressure control), 33 % (LDL control for cholesterol), 35 %, (aspirin recommendation), and 20 % (smoking cessation referral). The number of patients that will be eligible in each 3-month period is based on an average physician roster of approximately 1,000 patients. Currently, 30 % of those patients have hypertension, 30 % have hyperlipidemia, and 20 % smoke. If we make a conservative estimate that 25 % of the patients will have an office visit per 3-month period, each eligible category will range from 50 to 75 patients. In Table 4, we use the lowest (most conservative) assumption of 50 patients, which reflects the likely size of the smoking group. At this level of eligible patients, we will have over 80 % power to detect a 2.2 % change, assuming a starting compliance rate of 20 % (increasing from 20.0 to 22.2 %) and between-site variance of 0.10 on the log scale.

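### The main-text power claim for the 12-month test is not supported by the Appendix it cites, which simulated an earlier quarter and a larger effect

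*Protocol article*

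**What the plan says.** **Analysis plan, Aim 1.** Each of the four outcomes is "tested separately with a two-sided test with *α* = 0.05". The time point is explicit: "Our primary outcome of interest for each of the four models is proportion of patients who meet clinical goals (described above) at 12 months". The null hypothesis is beta2 + 3·beta3 = 0, the fourth intervention quarter.

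**Power/effect size analysis, main text.** The quantity of interest is compliance "in the fourth quarter of the PF intervention (i.e., month 12 of the intervention) relative to compliance proportions at baseline". Citing the Appendix, the section says "we will have over 80 % power to detect a 2.0 % change, assuming a starting compliance rate of 20" percent, that is 20.0 to 22.0%, with an average of 50 eligible patients per physician per quarter. It adds that power exceeds 95% if the between-site variance is nearer 0.01 or 0.05.

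**Appendix.** The comparison is "in the third quarter after PF intervention with the compliance proportion at baseline". The rate ratio is exp(beta2 + 2·beta3), and the simulation tested whether beta2 + 2·beta3 ("the effect size in the third quarter) was significantly different from 0") differed from zero. The result is: "we will have over 80 % power to detect a 2.2 % change, assuming a starting compliance rate of 20" percent, that is 20.0 to 22.2%, at variance 0.10. For a variance near 0.05 the Appendix says only that power rises substantially. It gives no percentage and does not mention 0.01.

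**The concern.** The coefficient on beta3 is 3 in the primary test and 2 in the simulation, so these are different hypotheses and not two labels for one. The effect sizes also differ: a ratio of 1.10 in the main text and 1.11 in the Appendix. Both differences lower power. The main-text effect is smaller, and carrying the exposure slope one quarter further makes the contrast noisier. Yet the same claim of over 80% is attached to both.

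This is the article's only power justification for its four primary hypotheses. If the figure is too high for the test that will be run, a null result in the scenario described would be read as stronger evidence against an effect than the design can give.

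**Working it through.** **Inputs from the article.** Two-sided alpha 0.05; 63 sites in each of four waves (252); baseline 20%; 50 eligible patients per physician per quarter; site variance 0.10 on the log scale; linear trend estimated. **Not given:** physicians per site and the quarters simulated. Table 4 was not available for this check.

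**1. Precision of the two contrasts.** I used the generalised least squares information for the log-linear model with a site random intercept and residual variance 1/(50 × physicians × 0.20) per site-quarter. Layouts tried were Table 1 with and without follow-up quarters, and common windows of 5, 8 and 12 quarters, each with 1 to 3 physicians per site. SE(beta2 + 3·beta3) / SE(beta2 + 2·beta3) was 1.22 to 1.28 throughout. Example: Table 1 with follow-up counted as exposed and 2 physicians gives 0.0429 / 0.0348 = 1.23.

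**2. Reproducing the Appendix.** Power ≈ Φ(log r / SE − 1.96). With a mix averaging 1.75 physicians per site, 1,000 simulated data sets per setting gave:

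| Appendix statement | Stated | Simulated |
|---|---|---|
| 20.0 to 22.2%, third quarter | over 80% | 84% |
| Same, 70 patients | 92% | 93% |
| 25.0 to 27.7% | 91% | 89% |

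The benchmarks also imply the anchor without a physician count, if SE scales as one over the root of the expected count.
- 92% at 70 patients: (1.960 + 1.405) × √(50/70) = 2.844, so Φ(0.884) = 81% at 50 patients.
- 91% from a 25% baseline: SE = 0.1026 / 3.301 × √(0.25/0.20) = 0.0347, and 0.1044 / 0.0347 = 3.00, so 85% at a 20% baseline.

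An anchor of 80–85% is therefore consistent with everything the Appendix text states.

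**3. From the anchor to the main-text claim.** log 1.11 = 0.1044 and log 1.10 = 0.0953. The third-quarter SE is 0.1044 / 2.802 = 0.0373 at 80% and 0.1044 / 2.996 = 0.0348 at 85%.

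| Case | Anchor 80% | Anchor 85% |
|---|---|---|
| Third quarter, 22.0% | 73% | 78% |
| Fourth quarter, 22.2% (SE × 1.28 to 1.23) | 59–62% | 65–68% |
| Fourth quarter, 22.0% (the claim) | 52–55% | 57–60% |

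The longer common windows (SE ratio about 1.225) reach 61%. Direct simulation with the 1.75-physician mix gives 58% for the claim. Even without the change of quarter, 22.0% falls short of 80%.

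**4. Effect detectable with 80% power, fourth quarter.** 20 × exp(2.802 × SE), with SE from 0.0348 × 1.23 = 0.0428 to 0.0373 × 1.28 = 0.0477, gives 22.6 to 22.9%.

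**5. What would rescue the claim.** Reaching 80% for 22.0% in the fourth quarter needs about 3.1 to 3.8 physicians per site. The Appendix case would then have about 97% power at 50 patients, above the 92% it reports at 70.

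**6. Without calibration.** Fourth-quarter power for 22.0% is about 34–42% with 1 physician per site, 53–64% with 2 and 69–78% with 3.

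**7. Lower variance** (1.75 to 2 physicians, Table 1 layouts with and without follow-up):

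| Variance | Appendix contrast, 1.11 | Primary contrast, 1.10 |
|---|---|---|
| 0.05 | 84–89% (up to 90% by simulation) | 58–66% |
| 0.01 | 96–98% | 75–86% |

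**The case against.** - **Only one scenario is affected.** A reader might infer that all four primary tests have little better than even power. The article does not support that. The Appendix calls 50 patients the likely size of the smoking group, gives baselines of 49% (blood pressure), 33% (cholesterol) and 35% (aspirin), and says power is higher for these. With 2 physicians per site and the control and intervention quarters of Table 1, fourth-quarter power at ratio 1.10 is about 57% for smoking, 78% for aspirin (50 patients assumed), 90% for cholesterol and 97% for blood pressure (75 patients for the last two). A ratio of 1.10 is a larger absolute change at those baselines, but the Appendix itself treats the ratio as the natural scale. This objection stands.
- **The size rests on missing inputs.** This also stands: 52–61% is a calibrated range, not a known value.
- **The modelled quarters are unsettled.** The outcome section says data are collected for the 12 months before the intervention, whereas Table 1 shows one to four control quarters. Modelling four pre-intervention quarters per site would give about 77–80% with 2 physicians and 71–75% with 1.75. So 52–61% is not established as the power of the final analysis.
- **The main text may rest on another run.** It reports 22.0% and variance 0.01, which the Appendix text does not. But it cites the Appendix, and no such run is described.
- **The effect may keep growing into the fourth quarter.** It may, but the main text fixes the fourth-quarter value at 22.0%.
- **Enrolment is 290 sites.** Those sites are there to allow for 15% attrition. Analysing all of them would add only a few points.

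**Conclusion.** Wrong as written. The mismatch of quarter, contrast and effect size can be read directly from the article and needs no assumption: the Appendix does not support the main-text statement.

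The size is conditional. For a 20% baseline, 50 eligible patients per physician and variance 0.10, and with the Appendix taken to show 80–85%, the primary contrast has roughly 52–61% power for 20.0 to 22.0%. Its 80%-power effect is about 20.0 to 22.6–22.9%. This assumes that the Appendix simulated a layout like those tried and that the reported benchmarks are right. It does not extend to the other three outcomes, whose power is higher.

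The figure of over 95% is plausible for the Appendix contrast at variance 0.01. At 0.05 it is not supported, and the primary contrast at ratio 1.10 falls short at both variances.

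**What to change.** Rerun the existing simulation for H0: beta2 + 3·beta3 = 0, with the 250 sites expected to be analysed and the control and intervention quarters that will actually be modelled. State the physicians-per-site distribution used. Then give the resulting power, or the detectable effect, identically in the main power section and the Appendix, including the values at variances 0.01 and 0.05, and say which outcome the scenario represents. The replacement figures should come from that rerun and not from the calibrated range here.

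The model, test and number of sites do not change. The cost is a rerun of existing code and, probably, a less favourable stated figure.

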### Study design

HHNYC is a stepped-wedge cluster randomized controlled trial that is designed to evaluate the implementation process and the impact of PF (intervention) compared to usual practice (control), on implementation of the Million Hearts ABCS treatment guidelines in 250 primary care practices. All practice sites begin as part of the control condition and are block-randomized into four waves with each wave beginning 3 months after the start of the prior wave and lasting for 12 months (see Table 1). All clusters eventually receive the intervention, and outcomes will be measured every 3 months in all clusters. We anticipate, conservatively, a 15 % attrition rate; therefore, we have enrolled 290 sites to ensure that enrollment of the required 250 sites is achieved at the end of the study. This study has received Institutional Review Board approval by the New York University School of Medicine.

**Table 1 Tab1:** Stepped-wedge study design

	Year 1 (months)				Year 2 (months)				Year 3 (months)			
Clusters	3	6	9	12	15	18	21	24	27	30	33	36
	Time period											
1 (80 sites)		C	X	X	X	X	F	F				
2 (70 sites)		C	C	X	X	X	X	F	F			
3 (70 sites)		C	C	C	X	X	X	X	F	F		
4 (70 sites)		C	C	C	C	X	X	X	X	F	F	

*C* control period, *X* intervention period, *F* follow up period

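### Aim 2 tests site characteristics as modifiers of PF in a model with random intercepts only, so if sites also differ in their response to PF for other reasons, the interaction standard errors are too small

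*Protocol article*

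**What the plan says.** The Aim 2 text tests moderation by "including separately each organizational characteristic in the main models used under Aim 1 as a main effect and in interactions with the PF indicator". The characteristics it names, adaptive reserve and change capacity, are baseline values with one value per site.

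The model being reused is set out under Analysis plan, Aim 1: "we will use a Poisson model with random site and provider within site effects". Equation (1) shows one scalar site term, b_i. The sentence defining it is garbled and appears to attach "is a random effect for site" to the offset, but b_i with variance σ_b² is clearly meant. The PF terms β2 and β3 are common to all sites. They describe an effect that "allows for the intervention effects to grow over time following implementation of the intervention", but not one that differs between sites. The Appendix simulates from the same structure. Neither aim mentions a random PF effect or a cluster-robust variance.

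Under Study design, "outcomes will be measured every 3 months in all clusters". Table 1 gives each site one to four control quarters and four intervention quarters.

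Two other sections bear on whether sites respond alike. Internal and external context says that 20 interview sites will be picked to span differing responses in patient outcomes. The Discussion regards variation in implementation fidelity as likely.

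**The concern.** Whether the PF effect changes with a site characteristic is a comparison between sites, so the information comes from about 250 site-level before-and-after contrasts. A random intercept takes out differences in level between sites. It is constant across control and PF quarters, so it cannot take out differences in response. A provider-within-site intercept is constant in the same way and does not help.

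Given the intercepts, the model treats a site's intervention quarters as independent evidence on the interaction. Any difference in response that the tested characteristic does not explain is set to zero. Because characteristics are entered one at a time, the influence of every other real moderator is left unmodelled in each test. If such differences exist, the standard error of the interaction is too small and an unrelated characteristic can look like a moderator. Aim 2 is one of the four specific aims, so its moderator findings are a main product of the trial.

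**Working it through.** **Inputs from the article.** Sites: "we assumed 63 sites in each stratum, for a total of 252 sites". Baseline rates: "The current baseline compliance rates for the four measures are 49 % (blood pressure control), 33 % (LDL control for cholesterol), 35 %, (aspirin recommendation"), and 20 % for smoking. Eligible patients: 50 to 75 per physician per quarter. Site-intercept variance: 0.10. Quarters: Table 1.

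**Assumptions.** Tau is not given, so a range of 0 to 0.3 is shown. Physicians per site are not given. I take either one per site, or a mix of 50 %, 20 %, 15 % and 15 % with one to four physicians (mean 0.5 + 0.4 + 0.45 + 0.6 = 1.95). The two-sided 5 % level is stated for Aim 1 and is assumed to carry over to Aim 2.

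**Reproducing the stated figures.** The article gives no operating figure for Aim 2, so the simulation was first checked against the Appendix power for Aim 1, with the 1.95 mix:

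| Setting | Stated | Simulated |
|---|---|---|
| 20.0 to 22.2 %, 50 patients | over 80 % | 85.6 % |
| same, 70 patients | 92 % | 91.8 % |
| 25.0 to 27.7 %, 50 patients | 91 % | 89.3 % |

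With one physician per site the first power is about 63 %, so the agreement depends on the physician count.

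**Closed-form approximation.** Take site i with mean count m_i per quarter, c control quarters and 4 PF quarters. The log contrast PF minus control has Poisson variance v_i = (1/m_i)(1/c + 1/4). The planned model weights sites by w_i = 1/v_i. If responses also vary with SD tau, then

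true variance / model variance = 1 + k·tau², with k = Σw²/Σw.

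- For c = 1, 2, 3, 4, let g = 1/(1/c + 1/4) = 0.80, 1.33, 1.71, 2.00. Then Σg²/Σg = 9.36/5.85 = 1.60.
- For the mix, E[n²]/E[n] = 5.05/1.95 = 2.59.
- k = rate × patients × 2.59 × 1.60. Smoking: 0.20 × 50 × 2.59 × 1.60 = 41.4. Cholesterol: 0.33 × 75 × 2.59 × 1.60 = 102.6. Blood pressure: 0.49 × 75 × 2.59 × 1.60 = 152.3. Smoking with one physician per site: 0.20 × 50 × 1.60 = 16.0.

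The false-positive rate is 2[1 − Φ(1.96/√ratio)]. For smoking at tau = 0.20, the ratio is 1 + 41.4 × 0.04 = 2.66, its root is 1.63, 1.96/1.63 = 1.20, and the rate is 22.9 %. The formula ignores the time trend, the growth term and the rise in counts under PF.

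**Simulation, Poisson counts** (600 data sets per cell, variances estimated, irrelevant standard normal characteristic; approximation in brackets):

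| Tau | Smoking, 1 physician | Smoking, mean 1.95 | Blood pressure, mean 1.95 |
|---|---|---|---|
| 0 | 3.5 % (5.0) | 4.5 % (5.0) | 5.3 % (5.0) |
| 0.05 | 6.3 % (5.5) | 4.8 % (6.2) | 11.3 % (9.5) |
| 0.10 | 6.8 % (6.9) | 11.3 % (9.9) | 25.0 % (21.7) |
| 0.20 | 12.2 % (12.6) | 23.0 % (22.9) | 50.5 % (46.2) |
| 0.30 | 22.7 % (21.0) | 39.7 % (36.7) | 62.2 % (60.9) |

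With a random site PF effect added, every cell fell between 3.3 % and 7.0 %.

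**Bounded counts.** Real counts cannot exceed the number eligible, so the Poisson variance is too large and partly offsets the problem. In the approximation the ratio becomes (1 − rate) + k·tau². At tau 0.05, 0.10 and 0.20 this gives 3.9, 7.5 and 21.1 % for smoking; 4.2, 13.2 and 37.0 % for cholesterol; and 3.8, 16.9 and 44.6 % for blood pressure.

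Binomial simulations agree:
- Mean 1.95 physicians, 50 patients, site variance 0.05: 7.4 % (20 % baseline) and 7.6 % (35 %) at tau 0.10; 23.4 % and 32.0 % at tau 0.20. With the random PF effect, 4.0–5.8 %.
- One to three physicians with equal chance, site variance 0.10, at tau 0.05, 0.10 and 0.20: smoking 3, 7–8 and 19–23 %; cholesterol (75 patients) 7, 12 and 38 %; blood pressure (75 patients) 4, 16 and 39 %. At tau = 0 the range is 1–4 %. With the random PF effect, 2–5 %.
- A further simulation with all variances estimated: 7–17 % at tau 0.10 and 23–41 % at 0.20, against 3–5 % with the random PF effect.

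**Reading tau.** The Appendix target of 20.0 to 22.2 % is ln(1.11) = 0.104. Tau = 0.10 is therefore an SD about equal to the mean effect: most sites' rates under PF would lie within 22.2 % × exp(±0.196), about 18 % to 27 %, and Φ(−1.04) ≈ 15 % of sites would worsen. At tau = 0.20, about 30 % would worsen.

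**The case against.** The strongest reply is that everything turns on a tau that the article does not contain. At tau = 0 the planned test is nominal or conservative, and at 0.05 with bounded counts there is essentially no inflation. With single-physician sites the smoking test is only mildly affected at 0.10 (6.8 % even with Poisson counts). At 0.20 the SD is twice the planned mean effect, which is a lot of heterogeneity. The blood pressure figure there is the least secure: with total SD √(0.10 + 0.04) = 0.374 and mean effect 0.10, (ln(1/0.49) − 0.10)/0.374 = 1.64, so about 5 % of sites would need a success probability above 1. All of this stands, and it makes the point conditional.

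A reader might infer that irrelevant characteristics will appear as moderators too often whatever the data, or that Aim 2 itself presupposes unexplained variation in response. The article supports neither. Aim 2 supposes only that response may vary with the characteristic tested, which the interaction models. Unexplained variation is made plausible by the interview-site selection and the Discussion, not asserted by Aim 2. Nor can one say that spurious moderators are likely to be reported. The article says that each of the four Aim 1 hypotheses "will be tested separately with a two-sided test with" α = 0.05, and gives no decision rule for Aim 2. How many characteristics and outcomes are tested is a separate multiplicity question.

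It can also be said that a condensed article leaves random-effects detail to the analysis plan, and equation (1) does omit the provider effect named in the text. But the article states which model Aim 2 reuses and describes its random effects, in text and equation, as intercepts. The proposal replaces a stated method; it does not ask for missing detail.

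Finally, the repair was not tested with growth after PF start that varies between sites, and the robust variance suggested below was not simulated.

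**Conclusion.** The point holds in conditional form. The Aim 2 interaction tests are valid only if each tested characteristic accounts for all between-site variation in the PF effect, and the article gives reasons to doubt that. If unexplained variation exists, the standard errors are too small. With bounded counts and about two physicians per site, a nominal 5 % test rejects an irrelevant characteristic in no more than about 7 % of data sets at tau of 0 to 0.05, about 7–17 % at 0.10 and about 20–40 % at 0.20. Smaller panels give less: for smoking with one physician per site, about 12 % at 0.20 even with Poisson counts. Pure Poisson counts give more for blood pressure (25 % and 50.5 % at 0.10 and 0.20), but that case is less realistic. These figures rest on assumed values of tau, physician numbers and the 5 % level. The direction of the error and the effect of the repair do not depend on the exact values. The change is worth making because it costs little and leaves the test close to nominal at every tau tried.

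**What to change.** In the Aim 2 models, add a site-level random effect of PF, correlated with the site intercept, and keep the provider-within-site effect. In lme4 this means (1 + I_PF | site) in place of (1 | site). Test each characteristic-by-PF interaction in that model. State in advance that if the fit is singular, the intercept-only result will be reported, with a site-level cluster-robust variance as a check.

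The cost is one model term and a sentence or two under Aim 2. Data collection and sample size do not change. The price is wider intervals for the moderator effects, a slightly conservative test when responses do not in fact vary, and occasional singular fits.
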